### Blinding

All patients will be treated in the acupuncture clinical research center and will not be informed of the type of treatment that they will receive. Outcome assessors, data managers and the statistician will be blinded in this trial. To preserve masking, only the acupuncturists will have access to treatment allocation [19, 20]. However, they must learn how to use the blinding method to communicate with participants to ensure treatment blinding. The blinding principle will be operated until the data are locked down. The questionnaires regarding blinding will be completed immediately after the 5th and 10th treatments, as well as at the end of the follow-up. The success of these blinding strategies will be appraised at the end of the study by the Blinding Index (BI).

### Interventions

Participants will be randomized to the five treatment groups and receive ten sessions of treatment over a period of 5 weeks. Acupuncture treatment will be performed by a senior acupuncturist who has held a practitioner licence for more than 10 years. The participants will be asked to rest for 15 min before treatment. A constant room temperature of 23 to 25 °C will be maintained to ensure the patients are comfortable and relaxed during treatment. Subjects will be advised to lie in the prone position on the treatment couch. Interventions will be performed twice a week from Monday to Friday. Each session will last for 20 min.

The combinations of EX-HN 15 and SI 15 will be selected for the different groups based on the academic literature [21]. EX-HN 15 is an acupoint on the neck, 2 cun (1 cun is equal to the width of the patient’s thumb knuckle stripe) above GV 14 (*Dazhui*), and 1 cun lateral to the posterior median line. SI 15 is located on the back, under the 7th cervical vertebra and 2 cun lateral to GV 14. According to TCM theory, stimulation of EX-HN 15 and SI 15 can remove meridian stasis by promoting the circulation of “Qi” and blood to relieve neck pain. After the skin is sterilized with disposable 75% alcohol swabs, a sterile needle (length: 25 mm, diameter: 0.30 mm; Huatuo, Suzhou Medical Supply Factory Co., Ltd., Suzhou, China) will be inserted. The needle-punching depth in the acupoint will be 0.5 to 0.8 cun. The needle will be manipulated by lifting and twirling until the participant feels a sensation (denominated *de-qi*).

The needle in the non-acupoint will be inserted without the use of acupuncture techniques during the experiments. Non-acupoints 1 and 2 are located 1 cm lateral to EX-HN 15 and SI 15. The shallow puncture is just enough to maintain the needles in a fixed position and not enough to produce *de-qi*. For subjects receiving sham puncture, “Streitberger” needles (Asiamed Inc., Bridport, UK) with blunt tips will be used in the same areas as those in the treatment group, but will not pierce the skin. The needles will then be fixed and retained for 20 min. The treatment details in each group are illustrated in Table 1.

**Table 1 Tab1:** Treatment details of each group

Group	Acupoint	Manipulation
Group A traditional acupuncture	EX-HN 15 (*Jingbailao*)	The needle-punching depth in the each acupoint is 0.5 to 0.8 cun. The sensation (denominated *de-qi*) is necessary
	SI 15 (*Jianzhongshu*)	
Group B acupoints shallow puncture	EX-HN 15 (*Jingbailao*)	The needles are pierced through the skin for 0.2 cun and not enough to produce *de-qi*
	SI 15 (*Jianzhongshu*)	
Group C non-acupoint acupuncture	Non-acupoint 1	The needle-punching depth in the acupoints is 0.5 to 0.8 cun. The sensation (denominated *de-qi*) is necessary
	Non-acupoint 2	
Group D non-acupoint shallow puncture	Non-acupoint 1	The needles are pierced through the skin for 0.2 cun and not enough to produce *de-qi*
	Non-acupoint 2	
Group E sham puncture	EX-HN 15 (*Jingbailao*)	The placebo needle tip is pressed and fixed on the skin of the acupoint
	SI 15 (*Jianzhongshu*)	

### Outcome measurements

#### Primary outcome measurement

##### Neck Pain Scale

The Northwick Park Neck Pain Questionnaire (NPQ) has been widely used in research and has been shown to have high validity and reliability for neck pain measurement [22]. It is comprised of nine items including the degree and duration of pain, symptoms including numbness, sleep and social activities, and quality of life aspects. The highest score is 100 and high scores indicate severe damage due to neck pain. The NPQ will be completed after each treatment and in the follow-up period.

#### Secondary outcome measurement

##### Pain threshold

A patient’s pain threshold (PT) is a semi-objective outcome and will be measured twice after each treatment. The PT measuring device (EP601C, East China Normal University of Science and Technology, Guangxi, China) has a 5-mA range. The positive electrode (anode) of the device is placed in the area of pain, and the other electrode is placed on the leg. According to the staircase method, the stimulus selection procedure with an increasing sequence of current stimulation from 0 mA in 2-mA steps will be presented to the patient. The patient will control the switch and press the stop key once they feel pain. The current strength (mA) on the screen will be recorded and the sequence direction will then be reversed. The descending sequence will be stopped when the participant feels pain, and the sequence points will be reversed again [23]. Three measurements will be recorded and the average PT calculated for each patient. PT will be assessed before and after treatment and the mean value calculated after the 5th and 10th treatments.

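### The pain-threshold procedure does not work as written: 2-mA steps on a 5-mA device allow readings of only 2 or 4 mA, and the descending run's stop rule gives no information

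*Protocol article*

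**What the plan says.** All the relevant text is in the Pain threshold section, under Secondary outcome measurement.

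- **Device:** it "has a 5-mA range".
- **Ascending run:** "an increasing sequence of current stimulation from 0 mA in 2-mA steps will be presented to the patient".
- **Stop rule for the ascending run:** "The patient will control the switch and press the stop key once they feel pain".
- **Recording and reversal:** "The current strength (mA) on the screen will be recorded and the sequence direction will then be reversed".
- **Descending run:** "The descending sequence will be stopped when the participant feels pain, and the sequence points will be reversed again".
- **Averaging:** "Three measurements will be recorded and the average PT calculated for each patient".
- **Timing, first sentence of the section:** pain threshold "will be measured twice after each treatment".
- **Timing, last sentence of the section:** "PT will be assessed before and after treatment and the mean value calculated after the 5th and 10th treatments".

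The Background presents pain threshold, together with the pain diary, as a semi-objective outcome meant to reduce reliance on subjective results. The Statistical analysis section compares subjective and semi-objective continuous outcomes between groups by ANOVA.

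**The concern.** Three features of the procedure do not fit together.

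1. The step is large against the device range, so very few current levels are available.
2. A staircase needs a descending endpoint that differs from the ascending one. Here both runs stop on the same event.
3. The first and last sentences of the section describe different measurement occasions.

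Pain threshold is the only outcome in the trial taken with an instrument; the others are questionnaires and a diary. If assessors follow the text literally, the measure meant to complement self-report becomes coarse and is cut off at the top. Real differences between arms would then be harder to see. Another team also could not reproduce the descending part of the procedure.

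**Working it through.** The plan states no expected value, standard deviation or target difference for pain threshold, so there is no figure of its own to reproduce. The check applies the written rules as they stand.

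**Inputs (all from the Pain threshold section):** start 0 mA; step 2 mA; range 5 mA, read as a maximum of 5 mA; both runs stop when pain is felt; three readings averaged.

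**Step 1: reachable levels.** Levels are 0 + 2k mA, subject to 2k ≤ 5. This gives k = 0, 1, 2, that is 0, 2 and 4 mA. The next level, 6 mA, exceeds the range. The step is 2/5 = 40% of the range.

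**Step 2: a single ascending reading.** The reading is the first level at or above the true threshold T.

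| True threshold T (mA) | Ascending reading (mA) |
|---|---|
| 0.5, 1.5, 2.0 | 2 |
| 2.5, 3.5, 4.0 | 4 |
| 4.5, 4.9 | none |

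For T up to 4 mA, the reading exceeds T by at least 0 and by less than 2 mA. Two patients with thresholds of 2.5 and 3.5 mA both read 4, so a 1-mA difference disappears. Two patients at 1.5 and 2.5 mA read 2 and 4, so a 1-mA difference appears as 2 mA. The top 5 − 4 = 1 mA of the range, or 1/5 = 20% of it, gives no reading.

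**Step 3: the average of three readings.** Each reading is 2 or 4, so the possible averages are:

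- (2 + 2 + 2)/3 = 2.00 mA
- (2 + 2 + 4)/3 = 2.67 mA
- (2 + 4 + 4)/3 = 3.33 mA
- (4 + 4 + 4)/3 = 4.00 mA

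The two middle values arise only if the reading changes from one repeat to the next.

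**Step 4: the descending run.** The direction reverses at a level that has just been felt as painful.

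- If the run starts at that level, the stop criterion is already met: 2 stops at 2, and 4 stops at 4.
- If it starts one step lower, that level was passed on the way up without pain, and every later level is lower still. With a stable threshold the criterion is never met.

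Either way, the descending run adds nothing to the ascending reading.

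**Step 5: timing.** The first sentence places two measurements after every treatment and none before. The last sentence requires a measurement before treatment, and a mean value after the 5th and 10th treatments. The text does not say which readings form that mean.

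**The case against.** **It may be a misprint.** The article condenses a fuller procedure and cites a source for it. A wrong step size and a lost negation in the descending rule would explain both oddities. For illustration only, a 0.2-mA step would give 5/0.2 = 25 non-zero levels. This is plausible, but nothing in the document shows it, and no other section gives a finer step, a wider range or a different descending rule. If it is a misprint, the text still needs correcting, and correcting the step alone would not repair the descending rule.

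**The analysed value is not two-level.** A reader might infer that pain threshold takes only two values. That holds for one reading. The recorded outcome averages three and can take four values. This part of the objection stands.

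**Loss of power is not quantified.** A reader might infer that the measure cannot detect any plausible difference between arms, or that ANOVA on it is invalid. The documents give no pain-threshold mean, standard deviation or expected difference, so neither can be shown. A shift in true thresholds still changes the share of patients reading 4 mA, and a comparison of means is not invalid because the measure is discrete. The contrast is weakened, not removed.

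**Bias between arms is not shown.** The ascending reading overshoots the true threshold, but the same procedure applies in every arm. Any average overshoot would need an assumed distribution of thresholds, which the documents do not supply.

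**Timing may be settled elsewhere.** The study schedule is in Fig. 2, which was not available for this check. It may fix the occasions, but the two sentences in the section would still disagree. A reader might also infer that pre- and post-session values are averaged together, which would halve an acute session effect. The text does not state such pooling; it only leaves the mean undefined.

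**Conclusion.** The procedure fails if followed as written. A single ascending reading can only be 2 or 4 mA, the average of three takes at most four values, thresholds above 4 mA go unrecorded, and the descending run is uninformative on either reading of its starting point. This rests on taking the 5-mA range as a 5-mA maximum and the 2-mA step literally. The descending-run fault depends on neither of those assumptions.

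The consequence is lost resolution and top-censoring in one secondary outcome, which weakens comparisons between arms by an amount the documents do not allow to be computed. The timing conflict is a lesser point of wording to be reconciled. The primary outcome (the Northwick Park Neck Pain Questionnaire), its analysis and the sample size are not touched. The correction should be made, but the trial's main conclusion does not depend on it.

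**What to change.** Amend the Pain threshold section as follows.

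1. Reconcile the step with the device range by stating the increment actually used, which must be small relative to 5 mA.
2. Define the descending endpoint as the current at which pain is no longer felt.
3. State one measurement schedule, consistent with Fig. 2, and say which readings enter the mean. Do not pool pre-session and post-session values.
4. If any readings were taken on 2-mA steps, flag them in the dataset.

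The cost is a text correction and brief retraining of assessors on the existing device. The Trial status section says recruitment is only beginning, so a prompt correction would cover most of the data.

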##### Short Form McGill Pain Questionnaire-2 (SF-MPQ-2)

This questionnaire is comprised of four parts including the Continuous (tender, cramping pain, aching pain, gnawing pain, heavy pain), Intermittent (splitting pain, shooting pain, sharp pain, stabbing pain, electric-shock pain, piercing), Neuropathic (hot-burning pain, cold-freezing pain, “pins and needles” or tingling, pain caused by light touch, itching and numbness) and Affective (tiring-exhausting, sickening, fearful, punishing-cruel) subscales [24]. The different aspects of pain evaluation and each item will be based on pain during the previous week. The scores are calculated by adding four different scores. High scores indicate worse neck pain.

##### Short-form 36-Item Health Survey (SF-36)

Health status will be evaluated using the Chinese version of the Medical Outcome Study Short-form 36-Item Health Survey (SF-36). The SF-36 will be used to test the correlation between health-related quality of life and related factors (sex, age, physical function and daily functioning) rated on a 5-point scale [25]. This survey will be performed before treatment, after the 5th and 10th treatments and at the end of the follow-up period.

##### Pain diary

The patients will be provided with neck pain diaries to report working time, attack times and duration of pain, accompanying symptoms and dosages of rescue medication. The patients will be instructed on how to use the diary to record information during treatment. Pain will be measured during the baseline period, after the 5th and 10th treatments and at the end of the follow-up period.

#### Follow-up

The researcher will contact the patients via telephone and a short messaging service. The follow-up period will be 3 months and monthly information will be collected. If participants discontinue the intervention protocols, the latest outcome data including changes in symptoms and medication compliance will be presented. The reasons for treatment failure will be recorded and analyzed.

#### Patient safety

Patient safety will be assessed before and after treatment to avoid adverse events (AEs) including local pain, bleeding, needle breakage, palpitations or dizziness. All unpremeditated attacks and unexpected effects will be recorded on the AE Report Form. The relationship between acupuncture treatment and AEs will be rated from 1 to 6 (1 = definitely related, 2 = probably related, 3 = possibly related, 4 = probably not related, 5 = definitely not related and 6 = unknown). A primary investigation and follow-up monitoring will be performed if AEs are reported.

#### Data monitoring and quality control

Information on demographics, neck pain duration, symptoms, curative effects and patient dropout will be recorded in the Case Report Form (CRF) at each visit. If patients quit the trial at any time, the reason will be clarified in the CRF and the dropout rate will be analyzed statistically. The files of all clinical cases will be monitored by the directors. Data will be collated and checked by two data managers. In addition, all patient data will be confidential.

In order to maintain trial quality, all researchers will receive professional training on the trial method, study technique and the method used for regular monitoring. The staff will be tested after training to ensure consistency of methods. Outcome assessments will be blinded to evaluate the recorded information during the study period. Any modifications and corrections on compliance should be discussed in compliance with standard operation procedures and recorded. The monitoring information will be regularly submitted to the directors.

#### Sample size calculation

Following an academic literature review, a pilot study on acupuncture and its analgesic effect in CNP was identified [26]. The NPQ will be used as the primary outcome measure in assessment of the analgesic effect of acupuncture in this trial. Results from the pilot study with a two-arm design showed that the mean changes in NPQ were 20.71 ± 11.91 (acupuncture group) and 24.04 ± 11.83 (control group) [26]. However, our trial is a five-arm parallel-group study with the aim of assessing the efficacy of acupuncture. The mean ± standard deviation (SD) values reported in the pilot study will be used as the expected values in the treatment group and four control groups in the present study. PEMS 3.1 software was used to perform the sample size calculation. Thus, we calculated the appropriate trial sample size with 90% power, and the significance level was 0.05. The results showed that a clinically important difference was detected using a minimum sample size of 30 individuals in each group. With a maximum allowable dropout rate of 15%, a total of 175 subjects (35 per group) are being recruited.

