**Discussion:**

The purpose of this trial is to determine whether traditional acupuncture is more effective for chronic pain relief than sham acupuncture in adults with CNP, and to determine which type of sham acupuncture is the optimal control for clinical trials.

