## Background

Chronic neck pain (CNP) is a serious public health and socioeconomic problem worldwide. Studies have shown that the overall prevalence of CNP varies from 0.4 to 86.8% (mean 23.1%) [1]. The prevalence of CNP is greater among office workers than manual workers. This condition is characterized by activity limitations, dizziness, anxiety and insomnia [2]. Physical exercise, massage or physiotherapy, as well as education, have been proved to be efficient in reducing neck pain [3–6]. Acupuncture has also been well accepted as a non-pharmacological treatment for neck pain [7]. However, the treatment effect of acupuncture is moderate [8]. One argument is that “acupuncture is not associated with clinical effects beyond a powerful placebo response” [9, 10].

A growing body of research indicates that clinical trials of acupuncture have encountered many methodological challenges, including the identification of appropriate treatment and control groups, deficiencies in the blinding and follow-up of chronic pain [11]. Firstly, variable acupoints at different sites are commonly selected for the same disease in clinical practice. Based on our clinical experience, more than 20 acupoints have been selected as the main acupoints in neck pain. An appropriate repeatable treatment has not been established. Secondly, although shallow needle insertion and non-acupoints have been widely used in acupuncture research in sham groups, it has been suggested that these methods have therapeutic effects and are adjusted to accommodate different patients according to traditional Chinese medicine (TCM) theory [12]. The academic literature also indicates that the human body has more than 2200 singular points within formal naming beyond meridians [12]. The notion of a non-acupoint is obscure and there may be a role for specific factors of non-acupoints lateral to the acupoints [13]. Moreover, recent academic literature has shown that shallow puncture also produces analgesic effects in pain disorders. Thirdly, it has been reported that about 40% of subjects in these trials could distinguish non-penetrating sham acupuncture from real acupuncture [14].

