In view of these doubts, the influence of different needling points and depths should be investigated. First, the acupoints of local lesions including *Jingbailao* (EX-HN 15) and *Jianzhongshu* (SI 15) are commonly used in our hospital for neck pain [15]. The analgesic mechanism of acupoints on local lesions has been established in the spinal segments control theory to explain the gate control theory [16, 17]. According to the innervations of the pain focus, the effects of stimulation of EX-HN 15 and SI 15 on neck analgesia will be studied for feasibility and repeatability [15]. Second, several different groups of non-acupoints and shallow punctures will be established to determine whether traditional acupuncture is more effective for chronic pain relief than sham acupuncture in adults with CNP. The different depth and placement of needle insertion will also be investigated to determine efficacy [18]. Third, a single-blinded practice will be used and the adequacy of subject blinding will also be carefully assessed. The patients will be advised to lie in the prone position on the treatment couch and will be unaware of the treatment course in this trial. Data collection will be completed by the researchers over a 3-month follow-up period. Finally, we will assess the pain threshold (PT) and pain diary as semi-objective outcomes to avoid subjective results.

In this research, a randomized clinical trial will be performed to determine whether the outcome of traditional acupuncture treatment is significantly different to sham acupuncture in relieving CNP. We also aim to investigate which type of sham acupuncture is the optimal control for clinical trials.

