## Discussion

Acupuncture has been practiced for more than two millennia in China. In the practice of traditional acupuncture analgesia, it is generally acknowledged that structures and physiological functions are modulated by 14 energy meridians and the hypothetical “Qi” is usually translated as energy [30]. Acupuncturists with different experiences might have the different methods to operate *de-qi* (bring about the desired sensation) for the acupuncture intervention. Findings from clinical research strongly suggested that these specific differences of interventions have a major impact on the response to the curative effect [31]. Therefore, further trials are required to investigate the differences in these methods.

According to TCM theory, acupoints can be selected in three ways: an acupoint can be selected at a local lesion (with the pain area as acupoint *Shu*), far away from the local lesions, such as on limbs, and in accordance with symptoms. For non-acupoints at local lesions, the possible mechanisms of the analgesic effect may include the gate control theory triggered by neural pathways, alterations in local circulation and the immune environment [32]. Moreover, for shallow needle insertion, some researchers believe that shallow puncture can stimulate afferent nerves and activate the corresponding brain regions to produce a “limbic touch response” [33, 34]. Previous studies have also suggested that non-acupoints beyond the meridian and shallow puncture have an analgesic effect in subjects with fibromyalgia and other chronic pain conditions [35, 36]. Although the use of the “Streitberger” needle with a blunt tip has been supported in studies and reviews, it was reported that nearly half of the subjects could distinguish it from the real treatment in pain disorders [14, 37]. Therefore, further trials are required to investigate these differences. It is necessary to establish a standard for the control (sham) in clinical research due to the unknown analgesia mechanisms of traditional acupuncture.

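### The sample size plans for no difference among the four sham arms, so the stated 90% power does not cover the aim of finding the optimal sham

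*Protocol article*

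**What the plan says.** In the protocol article, the Sample size calculation section rests on a single source, a two-arm pilot. Its figures are given as follows: "mean changes in NPQ were 20.71 ± 11.91 (acupuncture group) and 24.04 ± 11.83 (control group"). The section then states that these values "will be used as the expected values in the treatment group and four control groups in the present study", and that "we calculated the appropriate trial sample size with 90% power" at a significance level of 0.05. The result is a minimum of 30 per group, raised to 35 per group (175 in total) for dropout of up to 15%.

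The four controls differ physically (Interventions, Table 1): shallow needling at the acupoints (B), needling at non-acupoints to the same depth as A (C), shallow needling at non-acupoints (D), and a blunt needle that does not pierce the skin (E).

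The Discussion paragraph of the Abstract gives, as one of two purposes, "to determine which type of sham acupuncture is the optimal control for clinical trials". The Background closes on the same note: "We also aim to investigate which type of sham acupuncture is the optimal control for clinical trials".

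On whether the shams are inert, the Background says of shallow insertion and non-acupoints that "it has been suggested that these methods have therapeutic effects", and describes the analgesic effect of shallow puncture as having been shown. The main Discussion reports earlier suggestions that "non-acupoints beyond the meridian and shallow puncture have an analgesic effect in subjects with fibromyalgia and other chronic pain conditions".

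The Statistical analysis section compares groups by ANOVA, with a P value of 0.05 or less counted as significant.

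**The concern.** One control mean for four controls amounts to planning for B = C = D = E. That sits badly with an aim of choosing among them, and with a rationale that expects at least some of them to be active. The text attaches a single power figure to the five-arm design, and a reader could take it to cover both aims.

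The risk lies in interpretation. The plan sets no expected difference among the shams, so a non-significant ANOVA is the likely outcome for any modest true difference. It could then be reported as showing that the shams are interchangeable, or that one of them is inert. The trial is meant to guide the choice of control in later trials, so such a misreading would carry forward.

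**Working it through.** **Inputs from the Sample size calculation section.** Acupuncture 20.71 (SD 11.91); control 24.04 (SD 11.83); 30 per arm, or 35 with no dropout; significance level 0.05. Sidedness is not stated, so I take it as two-sided. The SD for every sham arm is 11.83, as the plan assigns it.

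**1. The plan's own figure.** Difference = 24.04 − 20.71 = 3.33. Pooled SD = √((11.91² + 11.83²)/2) = 11.87. For 90% power, n per arm = 2 × (1.960 + 1.282)² × 11.87² / 3.33² ≈ 267.0, which rounds up to 268. The stated 30 is not reproduced. At n = 30 the noncentrality is 3.33 / (11.87 × √(2/30)) = 1.09, and the noncentral t distribution on 58 df gives power of 0.188 (0.212 at n = 35). This holds for any single A-versus-sham contrast, A versus E included.

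**2. Planned sham-sham difference.** 24.04 − 24.04 = 0 for each of the six pairs. Under this assumption the probability of a significant result is the 5% error rate, and no sample size is defined for the second aim.

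**3. Precision of one sham-sham difference.** Half-width = t(0.975, 2n − 2) × 11.83 × √(2/n).
- n = 30: 2.002 × 3.054 = 6.11 points.
- n = 35: 1.995 × 2.828 = 5.64 points.

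At 30 per arm the half-width is 6.11 / 3.33 = 1.8 times the acupuncture-control difference quoted for the sizing.

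**4. Detectable sham-sham difference at 90% power.** The normal approximation gives (1.960 + 1.282) × 3.054 = 9.90. The noncentral t distribution gives 10.07 points at n = 30 and 9.30 at n = 35. At n = 30 that is 10.07 / 3.33 = 3.0 times the pilot difference.

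**5. Four-sham ANOVA.** Suppose E differs from B, C and D by the full 3.33. The squared deviations sum to 3.33² × 3/4 = 8.32. The noncentrality is 30 × 8.32 / 11.83² = 1.78. With the critical value F(0.95; 3, 116) = 2.68, power is 0.17.

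None of these figures includes an adjustment for multiple comparisons. Any adjustment would widen the intervals and lower the power.

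**The case against.** **The sizing may be meant only for the main question.** The section describes its own aim as assessing the efficacy of acupuncture and never claims 90% for ranking shams. Sizing a trial for its main question alone is ordinary practice. This stands, and it makes the remedy one of wording and scope rather than of sample size. It does not remove the point: the two aims are stated side by side, and the text does not say which contrast the power covers.

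**An optimal control is not only a matter of NPQ change.** The article worries that subjects can identify the non-penetrating needle, and it plans blinding questionnaires, a Blinding Index and a credibility comparison. A sham can be judged on those. This also stands, so the point is limited to the NPQ part of the aim.

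**The statements on analgesia are hedged.** Non-acupoint effects are only suggested; only shallow puncture is said to have been shown to work. This tension is therefore weaker than a flat contradiction. The mismatch with the stated aim does not depend on it.

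**Contrasts and intervals may be in an analysis plan that is not shown.** True, and their absence is not faulted here. What is faulted is the shared mean, which the article states outright.

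**Conclusion.** The point holds within limits. The sizing assumes identical shams, so its power statement does not extend to choosing among them. With 30 per arm, only sham-sham differences of about 10 NPQ points would be found reliably, and each difference would be estimated to about ±6 points. These figures rest on a common SD of 11.83, two-sided testing at 0.05 and no multiplicity adjustment.

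A reader might go further and infer that power is overstated specifically for A versus B, C or D, because those shams are active. The article does not support that as a finding. It does not say what the pilot control was; if that control was itself an active sham, any dilution is already inside the 3.33. The control is also printed as changing more than acupuncture, and if change means improvement, a more active sham would widen the planned gap. As an illustration only, if a sham halved a true 3.33-point benefit (an assumed share), the difference would be 1.67 and power would fall from about 19% to 8%. This is a conditional caution. The shortfall from 90% to about 19% on the pilot inputs applies equally to all four A-versus-sham contrasts and does not depend on sham activity.

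**What to change.** **Sample size calculation.** State that the calculation addresses acupuncture versus control only, and that the quoted power does not apply to comparisons among B, C, D and E. Do not attribute the pilot control to arm E, since nothing in the article makes that link. Do not leave the impression that 90% holds for A versus E: restate the power that the pilot inputs give at 30 per arm (about 19%). Say what the pilot control was and in which direction its change runs.

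**Abstract, Background and Statistical analysis.** Present the NPQ part of the optimal-control aim as secondary estimation. Report the B−E, C−E and D−E differences in NPQ change with 95% confidence intervals (expected half-width about 6 points), beside the planned Blinding Index and credibility results. E serves here as the non-penetrating reference arm, not as a stand-in for the pilot control. State that no sham will be called inert, interchangeable or optimal on the strength of a non-significant ANOVA.

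**Cost.** Wording changes and three intervals, with no extra patients or procedures. The price is a weaker claim for the second aim and a less favourable stated power.
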